
**Figure 2 F2:**
[figure not shown]
**Explanatory model for the prevention of the onset of depression by family physicians.** Component 1 (training of family physician) prepares the family physicians for the intervention and component 2 (communicating the level and risk profile of depression to the patient) initiates it. This leads to a new doctor-patient interaction, which triggers component 3 (building up a tailored bio-psycho-family-social intervention to prevent depression by family physicians) that activates and empowers the patient (component 5), and which increases the patient’s perception of self-efficacy. This can also be achieved by component 4 (offering the patient the booklet) at the first doctor-patient interview.

**Table 2 T2:** Differences between interventions to prevent the onset of depression evaluated so far in adults and the new intervention in primary care

**Characteristics**	**Other interventions**	**New intervention**
**Type of prevention**	Selective or indicated^1^	**Universal**^2^
**Orientation**	Psychosocial (cognitive-behavioral, interpersonal…) or psychoeducational	**Biopsychosocial** (primary care orientation) and based on level and risk profile of becoming depressed (**personalized**)
**Type of intervention**	Formal (fixed rules)	Not formal (**tailored rules**)
	Same number of sessions for all patients	Minimum of three interviews but no maximum
	Same components for all patients	Number of components involved tailored
**Who implements the intervention?**	Therapists or specialists in mental health (psychologist, psychiatric nurse…)	**Family physicians**
**Sample size**	Small	**Large**

^1^ Patients with a specific risk of depression, high risk or subclinically depressed.

^2^ Patients with a low, moderate or high risk of depression. To date universal interventions have been evaluated to prevent depression but only in children and adolescents.

### Quality control of the intervention

In order to control the satisfaction and adherence to the intervention we will undertake two quality controls. The first one will be from a subjective focus. After each interview to inform patients about their risk of depression, the FPs will have to answer four questions: Have I written the label “predictD” in the clinical chart? (yes/no); what is my level of satisfaction with this interview to report the risk of depression? (5-Likert response options); would I change anything in this interview? (open answer); and observations (open answer). All patients will be asked about their overall satisfaction with their doctor (5-Likert response options); and only patients receiving the intervention will respond to the question “What is your level of satisfaction with the last interview in which your doctor informed you about your risk of depression?” (5-Likert-5 response options or “I was not informed”). The second is from an objective focus: we will review the clinical charts to confirm that FPs have included the label “predictD” on the problem list and we will also collect the number and content of visits related to the intervention.

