### Randomized allocation

The randomization and allocation to the arms will be carried out according to the health center; that is, all FPs and patients from one health center will be included in the same arm. If the same health center has FPs in both the control and the intervention groups, the likelihood of the FPs in the control group becoming contaminated by the intervention group is high, since Spanish health centers generally work as a team. We aim to evaluate a new intervention for primary prevention of major depression, which in principle will be delivered at patient level by the FP; however, due to the nature of the intervention some components could be delivered at community level, so the contamination between patients in the control and intervention groups in the same health center is likely. Therefore we have decided on cluster randomization to avoid this possibility in patients and FPs.

The randomization of the 70 health centers to allocate them to the control or intervention groups will be done stratifying by city. Thus, we will have 35 health centers assigned to the control group and 35 to the intervention group, 5 and 5 respectively for each one of the seven cities participating in our study. The randomization will be undertaken centrally, from the coordinating center in Malaga, by an independent person outside the research group using closed and opaque envelopes.

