### Masking

In trials that evaluate psychosocial interventions it is not possible for professionals who provide the new intervention or for patients who receive it to be blind to it [53]. However, in our trial those who assess outcomes (interviewers) will be different and independent from those who provide the intervention (FPs). Moreover, the interviewers will be not informed of the patient’s status in the control or intervention group. Those who perform statistical analyses will also be blind to the intervention and control codes.

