### Follow-up

All patients enrolled in the trial will be evaluated at baseline, 6, 12 and 18 months. Interviewers trained and independent from the FPs providing usual care or the new intervention will administer the CIDI and the other questionnaires. FPs participating in the trial will complete a self-administered questionnaire at baseline.

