### Variables

#### Main outcome

Our primary outcome will be the cumulative incidence of major depression during 18 months of follow-up. We will use the section of depression of the CIDI [54,55], developed and validated by the WHO [56]. The CIDI is a fully structured diagnostic interview that provides current diagnoses according to DSM-IV categories. We will use it to estimate the onset of major depression in each prior 6-month period (0–6, 6–12, and 12–18 months). Interviewing in this way, at baseline, 6, 12 and 18 months, we will obtain the most accurate picture of the cumulative incidence of major depression.

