### The intervention for the control group

Patients in the control group will receive “usual care”; that is, the kind of care that FPs usually provide when they are unaware of the risk profile for depression in the patients. This means explicitly that the patients and FPs in the control groups will not be informed about the risk profile at any point. FPs in the control group will not receive the training workshop.

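### A patient question restricted to the intervention arm would disclose allocation to the masked CIDI interviewers if they are the ones who ask it

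*Protocol article*

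**What the plan says.** Four statements in the Protocol article bear on the point.

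- **Masking:** physicians and patients cannot be blind, but "the interviewers will be not informed of the patient’s status in the control or intervention group".
- **Follow-up:** trained interviewers, independent of the family physicians, "will administer the CIDI and the other questionnaires" at baseline, 6, 12 and 18 months.
- **Quality control of the intervention:** "All patients will be asked about their overall satisfaction with their doctor", but for a second item, on satisfaction with the last interview about depression risk, "only patients receiving the intervention will respond to the question". That second item has a response option for patients who were not told their risk.
- **Randomized allocation:** "all FPs and patients from one health center will be included in the same arm".

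Two further statements matter. Under the control intervention, "the patients and FPs in the control groups will not be informed about the risk profile at any point". On the CIDI, Main outcome says "We will use it to estimate the onset of major depression in each prior 6-month period", so the primary endpoint depends on what these interviewers record.

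**The concern.** With physicians and patients both unmasked, masked CIDI interviewing is the main protection of the primary outcome against assessment bias. An item given to one arm only cannot be administered without knowing the arm, and its content concerns something that happens only in that arm. If it belongs to the interviewers' set, the plan itself builds disclosure into data collection. That differs from the chance remarks by patients that any open trial has to accept.

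At stake is the difference in cumulative incidence of major depression. If knowledge of the arm led interviewers to record fewer cases among intervention patients, the error would favour the intervention. The one bias whose direction the Strengths and limitations section states, contamination, is said to run the other way.

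**Working it through.** No stated figure decides this point, so the main check is to read the sections together.

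1. *Does the item identify the arm?* Yes. Control patients are never told their risk, and the general satisfaction item goes to everyone, so the restriction of the second item is deliberate. Its presence marks the intervention arm and its absence marks control.
2. *Who asks it?* The quality-control section does not say. Follow-up is the only place that assigns the patient questionnaires, and it assigns them to the interviewers. The article says so where self-completion is meant, as for the physician questionnaire. No section describes another person or route for this item. That the interviewers ask it is therefore an inference, though the natural one.
3. *How far would disclosure reach?* One centre means one arm, and Sample size plans 48 patients per centre. An interviewer who learns the arm from one patient knows it for every other patient of that centre whom he or she sees, then and later. How interviewers are assigned to centres is not stated, so the reach can be anything from one patient to the whole centre.
4. *Would asking it after the CIDI help?* Only for that patient's assessment at that visit. Later visits, and centre-mates not yet seen, would remain exposed.

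**Illustration of size.** The 12% incidence and the 5-point target come from Sample size. The under-recording fraction *s* in the intervention arm is an assumption with no source in the documents. With no true effect, the spurious difference is 0.12 × *s* if all three follow-up CIDIs are affected. If only the 12- and 18-month CIDIs are affected and onsets are spread evenly over the three periods (also an assumption), it is 0.12 × (2/3) × *s*.

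| *s* | All three CIDIs | Share of 5 points | 12 and 18 months only | Share of 5 points |
|---|---|---|---|---|
| 5% | 0.6 points | 12% | 0.4 points | 8% |
| 10% | 1.2 points | 24% | 0.8 points | 16% |
| 20% | 2.4 points | 48% | 1.6 points | 32% |

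**Effect on the test, all three CIDIs affected.** The plan's design effect reproduces: 1 + (48 − 1) × 0.06 = 3.82. The effective size per arm is 1643 / 3.82 = 430. In a two-sided 5% normal-approximation test of two proportions, take p₁ = 0.12 and p₂ = 0.12 × (1 − *s*). For *s* = 10%, p₂ = 0.108, the difference is 0.012, and the standard error is √(2 × 0.114 × 0.886 / 430) = 0.0217. The rejection probability is Φ((0.012 − 1.96 × 0.0217)/0.0217) + Φ((−0.012 − 1.96 × 0.0217)/0.0217), about 8.6%. For *s* = 5% and 20% it is about 5.9% and 20.5%.

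**The case against.** The strongest reply is that the article never says the interviewers ask this item. It appears beside a physician form and a chart review, neither of which is interviewer work, and self-completion or separate staff would remove the problem. A journal article also commonly leaves the order and routing of forms to the full protocol. This stands in part. The point has to be conditional, and the absence of fieldwork detail is not itself a fault. What remains is a stated arm-restricted item that sits badly with a stated masking safeguard under the only stated assignment of patient questionnaires.

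Second, masking is exposed in other ways. Patients know they were told their risk and may mention it, and consent content differs by arm (Ethical considerations). So removing this item would not by itself guarantee masking. That is true, but it does not justify a planned disclosure on top of accidental ones.

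Third, the CIDI is fully structured, the interviewers are independent of the physicians, and the analysts are blind to the arm codes. The first two limit the room for biased recording. Blind analysis does not correct outcomes already recorded with knowledge of the arm.

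A reader might infer that masking is lost at all 35 intervention centres from the first follow-up visit, or that about a quarter of the target effect would be spurious. The documents support neither. The first needs the interviewers to ask the item and a fixed assignment of interviewers to centres, and neither is stated. The second takes a single unsourced rate of 10% and applies it to all 18 months.

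**Conclusion.** The point holds in conditional form. If the CIDI interviewers administer the arm-restricted item, it discloses allocation to them, contrary to the Masking section. Because allocation is by centre, the disclosure can extend beyond the patient being interviewed and to later visits. The inference about who asks it rests on the Follow-up section and is not contradicted elsewhere.

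The resulting bias in the primary outcome cannot be sized from the documents. The range of 0.4 to 2.4 points shows what modest differential recording would do. It rests on assumed under-recording of 5% to 20%, in the direction that favours the intervention, and for the lower set also on even onsets. It is not an estimate. The sections on masking, follow-up and quality control should be reconciled before follow-up interviews begin.

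**What to change.** Take the item out of anything the interviewers administer or see, by one of two routes:

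- an identical self-completed sheet for all patients in both arms, sealed by the patient and sent to the coordinating centre. The existing response for patients who were not told their risk lets controls answer.
- collection only after every 18-month CIDI at that centre is complete.

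Half-measures fail. If the interviewer asks both arms aloud, the answer still discloses the arm. If the item is asked after each patient's own 18-month CIDI, centre-mates not yet assessed can still be unmasked.

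Under either route, give interviewers no arm-specific forms, and say in the Masking section how the item is collected. Optionally, have interviewers record a guess of allocation at 18 months so that masking can be checked.

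The cost is one reformatted item, with no extra visits. The sealed sheet will lose some responses and puts to controls a question that may not apply to them. The late route leaves only the last risk interview to be rated, and from a longer recall.

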### Side effects of the intervention

It is possible that some patients will react with fear or worry when receiving information about their level and risk profile of depression, especially apprehensive patients or those that already have a high level of anxiety. If a patient does not want to receive this information he/she will not sign the consent and therefore will be excluded from the study. This will be valid for each evaluation point. As stated in component 5 of the intervention, we will train FPs to support those patients excessively worried by the information given. FPs are obliged to report any side effect that occurs during the intervention. We will also evaluate the impact of the predictD-CCRT intervention on anxiety symptoms through measurements of the PRIME-MD [63,64] at each evaluation point of the follow-up.

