**Methods/Design:**

This is a multicenter randomized controlled trial (RCT), with cluster assignment by health center and two parallel arms. Two interventions will be applied by FPs, usual care versus the new intervention predictD-CCRT. The latter has four components: a training workshop for FPs; communicating the level and profile of risk of depression; building up a tailored bio-psycho-family-social intervention by FPs to prevent depression; offering a booklet to prevent depression; and activating and empowering patients. We will recruit a systematic random sample of 3286 non-depressed adult patients (1643 in each trial arm), nested in 140 FPs and 70 health centers from 7 Spanish cities. All patients will be evaluated at baseline, 6, 12 and 18 months. The level and profile of risk of depression will be communicated to patients by the FPs in the intervention practices at baseline, 6 and 12 months. Our primary outcome will be the cumulative incidence of major depression (measured by *CIDI* each 6 months) over 18 months of follow-up. Secondary outcomes will be health-related quality of life (*SF-12* and *EuroQol*), and measurements of cost-effectiveness and cost-utility. The inferences will be made at patient level. We shall undertake an intention-to-treat effectiveness analysis and will handle missing data using multiple imputations. We will perform multi-level logistic regressions and will adjust for the probability of the onset of major depression at 12 months measured at baseline as well as for unbalanced variables if appropriate. The economic evaluation will be approached from two perspectives, societal and health system.

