How patients are informed about their risk of becoming ill (cardiovascular events, hip fractures…) determines the outcome of prevention efforts [98,99]. In the same qualitative study as mentioned above, we found that primary care patients are pleased to be informed of their risk for depression [97]. Communicating with patients about their level and risk profile for depression is very new as until now there have been no validated risk algorithms to predict its onset [33,34]. This is also “*the starting component*”, which will activate the other components of the intervention. Each FP will receive (at baseline, 6 and 12 months) a report with the information on risk from each of 24 patients not depressed at baseline (belonging to their usual patient list) who will be randomly selected and will provide informed consent to participate in the study. This report will include the likelihood of becoming depressed at 12 months and the patients’ responses to each of the risk factors included in the predictD-Spain equation [34]. An example of a report of a patient who has 24.4% of becoming depressed at 12 months is shown in Figure 1.

If a patient has a moderate or high risk level (2nd or 3rd tertile), the FP will arrange an appointment with the patient aiming to communicate his/her risk of depression. If a patient has a low risk (1st tertile), the FP will have the option to report by telephone or face to face depending on the patient’s preferences. If a visit is scheduled, this will last approximately 10 minutes. This process of transmitting risk information will be held at baseline, 6 and 12 months. Reports will not include information about major depression diagnosis by CIDI at 6 and 12 months; although we will recommend that FPs screen for depression if the risk of depression was moderate or high at 6 and 12 months. FPs will write down on the problem list (clinical chart) the label “*predictD*” in order to remind them on opening their clinical charts that patients are included in the program predictD to prevent depression. This will help to ensure that when patients see their FPs, regardless of the reason for the consultation, doctors will take into account the information on their risk of depression if applicable.

3) *Building up a tailored bio-psycho-family-social intervention to prevent depression by family physicians*

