## Discussion

### Ethical considerations

FPs who do not meet exclusion criteria will be asked to sign an informed consent form before health centers are allocated to the control or intervention group. Once the health centers are randomly assigned to the control or intervention groups, selected patients who do not meet exclusion criteria in the health centers of the control group will be asked for consent to follow-up and in the intervention group to receive the intervention and to follow-up. In each health center a research assistant will ask participants to sign informed consent forms. In brief, participants in the intervention group will be informed about the purpose of the trial, the expected duration of their participation, trial procedures, foreseeable risks or inconveniences, expected benefits, whom to contact for further information, their rights as participants, and that their participation is voluntary and that they may refuse to participate or withdraw from the trial at any time, without penalty or loss of benefits. Since the identity of patients will not be known at the time when randomization of health centers is to be carried out, it will not be possible to seek their consent in advance of randomization. Nevertheless, FPs will provide consent to participate in the trial; moreover, none of them will be involved as a researcher in this study, so there should not in theory be a conflict of interest. In view of the fact that so far there is no evidence that the new intervention being evaluated in this study is effective, and given that it is generally the responsibility of FPs to put the medical interests of their patients above all other considerations, this may be an appropriate choice [109].

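### Intervention patients who decline the risk information at 6 or 12 months are excluded from the study; the rule can act in one arm only and conflicts with the stated intention-to-treat analysis.

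*Protocol article*

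**What the plan says.** All places are in the protocol article.

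- **Side effects of the intervention**, on patients who may be worried by hearing their risk: "If a patient does not want to receive this information he/she will not sign the consent and therefore will be excluded from the study". The next sentence reads "This will be valid for each evaluation point".
- **Intervention, component 2 (communicating the level and risk profile)**: "This process of transmitting risk information will be held at baseline, 6 and 12 months".
- **The intervention for the control group**: "the patients and FPs in the control groups will not be informed about the risk profile at any point".
- **Ethical considerations**: centers are randomised first, and for patients "it will not be possible to seek their consent in advance of randomization". Consent then differs by arm: control patients "will be asked for consent to follow-up and in the intervention group to receive the intervention and to follow-up".
- **Abstract, Methods/Design**: "We shall undertake an intention-to-treat effectiveness analysis". The Statistical analysis section repeats this as intention-to-treat by multiple imputation with covariate adjustment.

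**The concern.** Refusing one component of the intervention is treated as leaving the trial. The refusal can arise only where the component is offered, that is, in the intervention arm. Under intention-to-treat, a patient already enrolled who declines part of the intervention is a patient with incomplete exposure, still followed and still counted in the allocated arm.

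Two things are at stake. The first is the primary comparison: if those who decline differ in depression risk from those who stay, the arms stop being comparable for a reason created by the protocol itself. The second is the harm assessment: the same section plans to follow anxiety with the PRIME-MD at each evaluation point, and excluded patients would leave that series too.

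**Working it through.** **Step 1. What the rule does at each time point.**

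| Time | Control arm | Intervention arm | Effect of the rule |
|---|---|---|---|
| Baseline | Consents to follow-up only | Consents to intervention and follow-up | A decliner is never enrolled: arm-specific recruitment after cluster randomisation |
| 6 and 12 months | No information offered, so no trigger | A decliner is excluded | An enrolled patient is lost from one arm only |
| 18 months | No communication planned | No communication planned | No trigger |

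The direct conflict with intention-to-treat is therefore at 6 and 12 months.

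**Step 2. Possible size.** The protocol gives no refusal rate and no figure for this bias, so there is nothing of its own to reproduce. Inputs from Sample size: control incidence p = 12%, target difference 5 points. Assumed: no true effect, a share q of the intervention arm removed, and decliners at RR times the risk x of those who stay.

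p = q·RR·x + (1 − q)·x, so x = p / (1 − q + q·RR).

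| q | RR | x | Spurious benefit (points) | Share of the 5 points |
|---|---|---|---|---|
| 2% | 2 | 0.12/1.02 = 11.76% | 0.24 | 5% |
| 5% | 2 | 0.12/1.05 = 11.43% | 0.57 | 11% |
| 5% | 3 | 0.12/1.10 = 10.91% | 1.09 | 22% |
| 10% | 2 | 0.12/1.10 = 10.91% | 1.09 | 22% |
| 10% | 3 | 0.12/1.20 = 10.00% | 2.00 | 40% |

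With RR = 1 there is no bias; with RR below 1 it runs against the intervention.

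**Step 3. Credit for onsets already recorded.** Step 2 discards decliners' whole 18-month risk. But the CIDI at 6 and 12 months records onset in the preceding six months, so a later decliner may already have contributed. Assume even onset over the three windows, decliners' recorded cases kept, and their case-free members dropped. With f = 1/3 (decline at 6 months) or 2/3 (at 12 months) and y = RR·x:

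observed incidence = [(1 − q)x + q·f·y] / [(1 − q) + q·f·y].

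- q = 10%, RR = 3 (x = 0.10, y = 0.30): at 6 months 0.100/0.910 = 10.99%, a gap of 1.01 points; at 12 months 0.110/0.920 = 11.96%, a gap of 0.04.
- q = 5%, RR = 2 (x = 0.1143, y = 0.2286): at 6 months 0.1124/0.9538 = 11.78%, a gap of 0.22; at 12 months 0.1162/0.9576 = 12.13%, a gap of −0.13, slightly reversed.

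The Step 2 figures are thus upper values for their own assumptions.

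**Step 4. What the planned methods would recover.**

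- Regression adjusts for the baseline predictD probability, which includes the SF-12 mental score, lifetime depression and psychotropic medication. It does not include the PRIME-MD anxiety diagnosis or anything after baseline.
- Inverse probability weighting uses baseline predictors only, so it cannot reflect a reaction to an earlier disclosure.
- Multiple imputation may add covariates that predict missingness, and anxiety is measured at every visit, so it could capture part of the mechanism. It relies on missing at random, and the text does not say that excluded patients remain in the imputed dataset.

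**The case against.** The case for leaving the text alone has several parts.

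- The sentence concerns consent, and lack of consent is an exclusion criterion in both arms (Table 1). This stands for baseline: someone who never enrols is not in an intention-to-treat set. What remains there is recruitment bias. Consent after randomisation is disclosed, and patient refusal is discussed in general under Strengths and limitations.
- The extension to each evaluation point might mean only that patients may withdraw at any time, and no re-consent at 6 or 12 months is described. That reading is possible, but the words attach to exclusion from the study.
- The Follow-up section has every enrolled patient evaluated at all four times, and the intervention patients' satisfaction item (Quality control of the intervention) includes an answer for not having been informed. Both suggest that uninformed patients may still be interviewed. Neither settles it: the first is general, and the second could cover a physician's omission. They show that the passages need reconciling.
- Refusal may be rare, since the article reports that patients welcome the information. This stands, and is why no size can be claimed.

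A reader might infer that the rule selectively removes higher-risk patients and so favours the intervention. The document does not show this. It says apprehensive or anxious patients may react badly on receiving the information, not that they will decline it. Nor would harm vanish from view altogether, because physicians must report side effects.

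**Conclusion.** Wrong as written. The text excludes enrolled patients at 6 or 12 months for declining the risk information, a trigger that exists in one arm only. This contradicts the stated intention-to-treat analysis and causes avoidable, possibly informative loss of primary-outcome and anxiety data. At baseline the same rule is a recruitment-bias risk and not a breach of intention-to-treat.

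Direction and size are open. With no true effect, 12% incidence, and 5–10% of the arm removed at 2–3 times the risk of the rest, the spurious benefit is at most about 0.6 to 2.0 points. All of these inputs except the 12% are assumptions. The bias shrinks, and in one example slightly reverses, when onsets already recorded are kept; it shrinks further if imputation and adjustment capture the reason for declining. The contradiction in the text does not depend on these figures.

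**What to change.** Reconcile Side effects of the intervention with the Abstract, Follow-up and Statistical analysis by separating refusal of the risk information from withdrawal from follow-up. State that an enrolled patient who declines the information at 6 or 12 months:

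- is recorded as not having received that component;
- stays in outcome follow-up (CIDI, SF-12, EuroQol, PRIME-MD and the cost inventory) unless consent to follow-up is itself withdrawn;
- is analysed in the allocated arm.

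This leaves the patient free not to hear the information. Interviewers are independent of the physicians, so outcomes can be collected without disclosure.

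For baseline, acknowledge arm-specific non-enrolment as a limitation. Applying the same willingness criterion to controls is a trade-off: they would have to be told about risk communication, whereas Strengths and limitations relies on their consenting to follow-up only to limit behaviour change.

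The cost is a changed sentence and a consent-form line, plus some dilution of the estimated effect. Even if 10% of the arm (assumed) lost all benefit, the planned 5 points would become 0.9 × 5 = 4.5. Patients who decline only later have had earlier communications, so the loss should be smaller.
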